## Specific objectives

To determine any significance in association between the FMHCP and antenatal care uptake, and facility delivery utilization in Ghana.To compare the difference in perinatal outcomes between Ghana and Kenya relative to the ‘free’ maternal health care policy.To measure the treatment effect of facility delivery on stillbirth, perinatal deaths, and neonatal mortality among women who received the FMHCP program compared to those who did not receive the program.To describe the ‘free’ maternal health care policy implementation in its current state in Ghana, within the context of funding constraints and implementation bottlenecks.

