**Fig. 2 Fig2:**
[figure not shown]
Trend of free maternal health care policy enrollment

**Table 1 Tab1:** Registration under the free maternal health care

Year	No. of enrollment	Percentage change
2008/2009	383,216	–
2010	504,609	24%
2011	485,460	− 4%
2012	754,658	36%
2013	774,009	3%
Total	2,901,952	

Source: NHIA Report, 2013

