## Operational definitions

*Utilization*: The use of maternal healthcare services rendered in a healthcare facility at any level.

*Maternal healthcare*: Antenatal care clinics and facility delivery services provided to pregnant women in a healthcare facility.

*Antenatal care uptake*: This refers to a 4+ antenatal care visit, thus, antenatal clinic visits of less than 4 are equal to zero visits (or 'no visit').

*Facility delivery*: This is when a pregnant woman gives birth in a healthcare facility at any level.

*Stillbirth*: This refers to the birth of a fetus with no signs of life, after 28 weeks of gestation or the death of a fetus within 24 h after birth.

*Perinatal death*: This refers to the number of stillbirth plus the death of neonates within the first week of life.

*Neonatal deaths*: This refers to the number of newborn deaths within 28 days of life.

*Treatment group*: Pregnant women study participants registered with the national health insurance scheme and made 4+ antenatal care visits or pregnant women participants in Ghana who delivered in a healthcare facility.

*Comparison group*: Pregnant women study participants registered with the national health insurance but have made less than 4 antenatal care visits with less than four minimum antenatal visits or pregnant women who did not deliver in a healthcare facility within the study period.

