## Methodology

### Study design

This study employs a mixed methodology in two-prongs. The first prong uses two quasi-experimental methods of a difference-in-differences (DID) analysis and propensity score matching (PSM) technique to analyze Demographic and Health Survey data sets of Ghana 2008/2014 and Kenya 2008/2014. Thus, the 2008 data set for the two countries forms the baseline data, while, the 2014 DHS data sets of countries, represents the end line data set.

The DID method necessarily requires comparable data sets from a different country, other than Ghana, that had not implemented the intervention (the 'free' policy) at the time, hence Kenya. The rationale for choosing Kenya is further explained below and will allow for comparison using data from a non-intervention country at the time, but with similar timelines data sets from DHS. This is also necessary for testing the parallel trend assumption applied in DID.

The propensity score matching (PSM) technique will also be used to estimate the average treatment effect on the treated through the generation of the propensity scores of the two groups; the treated group, post-intervention (2014 DHS) and the untreated group, pre-intervention data (2008 DHS) for comparison using the observed characteristics. The study then assumes that the unobserved characteristics are similar and cancels out, applicable in PSM.

The second prong of the study employs an intrinsic care study design to effect, collecting primary data through one-on-one in-depth interviews, and focus group discussion techniques from the Upper East Region of Ghana for analysis. Inductive thematic analysis will guide the management of the qualitative data using INVIVO 12, with vivid quotations to convey participants’ impressions.

The mixed-method design is driven by the overarching goal of the study; first to measure the free maternal healthcare policy effect on maternal healthcare utilization and to determine the impact of the utilization on stillbirth, perinatal death, and neonatal mortality.

Secondly, the study aims to explore an in-depth understanding of the policy in practice under its current operational constraints to explain policy workability from user and service provider perspectives. Figure 3, presents the diagrammatical representation of the study design.

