### Statistical methods and rationale

The design and intentions of the ‘free’ policy could not allow for randomization, the gold standard for impact evaluation, hence, quasi-experimental methods; DID and PSM techniques are adopted for the analysis of the secondary data sets. These methods are considered appropriate in evaluating public health programs that have no randomization in the policy design and implementation stages, and in particular, suitable for policies whose choice of participation is somewhat open and voluntary.

Combining the two methods gives the advantage of one making up for the limitations posed by the other. The DID analysis will employ the 2008 data sets of the two countries as baseline data (the starting time), whereas the 2014 DHS data sets of the same will represent the end line (the end time), as shown in Table 2.

**Table 2 Tab2:** Difference-in-differences method

	Before treatment	After treatment	Difference
Treatment (T)	X_0_	Y_0_	T = Y_0_–X_0_
Comparison (C)	X_1_	Y_1_	C = Y_1_–X_1_
Difference	X_0_–X_1_	Y_0_–Y_1_	DD = (Y_0_–X_0_) – (Y_1_–X_1_) = T-C

The choice of propensity score matching technique is also appropriate for the estimation of the policy average treatment effect through the generation of comparators ex-post. A drawback of PSM is the risk of lack of common support for paring treated units to the untreated. This particularly occurs when the sample size is small, so-called the curse of dimensionality. However, this study will merge the 2008/2014 data sets to increase the sample size and to minimize the risk of the curse of dimensionality [49].

Increased sample size will also enhance the study power for precision, albeit, also determined in the original two-stage DHS sampling design. The combined effect of the two quasi-techniques will eliminate the limitation of one and enhance the robustness of the study results [64, 65].

From Table 2 above, before treatment (baseline) is represented be GDHS 2008 (X_0_) for the treatment, T, and KDHS 2008 (X_1_) for the comparison group, C. The after treatment (end line) is also represented by Y_0_ and Y_1_ for Ghana DHS 2014 and Kenya DHS 2014, respectively. Thus, the DID analysis is the difference of T = (y_0_–x_0_) and C = (y_1_–x_1_); estimate for the before treatment difference and the after-treatment difference. The differences between the two represent the treatment effect, thus, the treatment effect is = (y_0_–*x*_*0*_) − (y_1_–*x*_1_), which is equal to T-C.

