### Demographic and health survey data

Demographic and Health Survey data sets are a household survey collected using a two-stage sampling method. Clusters for the sampling in Ghana used sampling frames of the 2000 and 2010 population and housing census to sample for the 2008 and 2014 DHS surveys respectively. For 2008, 412 clusters were determined in the first stage. In the second stage, 29 households were selected from each of the 412 clusters. Household from one cluster data was left out due to ethnic conflict at the time, thus 12, 323 households were selected.

The 2014 DHS also determined 427 clusters; 216 urban areas and 211 rural areas. The second stage then sampled 30 households per cluster for questionnaire administration in each household, thus, 12,831 households, similar to the sampling technique for the 2008 DHS.

In both situations, women between the ages of 15 and 49, who were either permanent residents in the selected households or stayed in the household the night before the selection were eligible to participate in the study and had their blood pressure measured. Sampling excluded women living in barracks, hotels, and prisons. Children between 0 and 59 months were also eligible and had their height and weight checked.

Eligible women participated in the study and answered questions on; age, pregnancy status, education, and relationship to the household head, residence, birth history, parity, pregnancy outcomes, knowledge and use of family planning methods, malaria interventions, diarrheal diseases, antenatal care and facility, and facility delivery (children born within the last 5 years).

Whereas GDHS 2008 collected data on the NHIS, the GDHS 2014 collected information on the free maternal health policy. Ghana and Kenya DHS surveys are similar in sampling procedures and methods and therefore comparable. DHS surveys are considered alternative to population and housing census in many situations due to their wide range of coverage in public health and socio-economic variables.

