### Data analysis

The secondary data will be cleaned and organized, dropping irrelevant variables and renaming covariates for ease of reference as necessary. Essentially, variables of interest in this study are binary outcomes i.e. 1 = case/the presents of an intervention, and 0 = no case, the absence of intervention, control.

Both multivariate logistic regression and Poisson with robust standard error, or negative binomial regression depending on whether there is over dispersion (conditional variance exceeding the conditional mean) will be fitted and analyzed. Thus, **loge** {*p*1 / *(1—pi)*} = *b0* + *b1 Xi1* + *b2 Xi2* + … + *bkXik*. The Use of the multiple logistic regression model also comes with the advantage of adjusting for confounding by including the covariates in the model.

For the matching method, Ghana’s DHS data sets (2008 and 2014) will be merged. This will increase the sample size to n = 8876, and add power to the study. The merger will also eliminate the risk of lack of common support, the so-called curse of dimensionality, a common phenomenon in propensity score matching, where treated units propensity scores cannot find suitable pairs.

Descriptive data will be presented using tables, frequencies, and proportions. The data will then be analyzed distinctly, using multiple statistical models and quasi-experimental design techniques. Firstly, the student independent *t*-test will be used to test for proportions, the significance of association, and mean differences between the independent variable, and the binary outcomes of interest; antenatal care uptake, and facility delivery utilization.

Test of association set < 0.05 less of significance, between the secondary variables of interest (stillbirth, perinatal death, and neonatal mortality) and the covariates; mothers age, marital status, level of education, wealth index, region, area of residence, twin delivery, parity, and employment status will be determined by using the Rao Scot Chis-square, which has an added sensitivity advantage, while adjusting for complex survey design features (weighting, clustering and stratification).

Only covariates found to be significantly associated with the dependent or independent variables will then be included in a multiple logistic regression model and adjusted for confounding [72].

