Logistics regression is considered appropriate, giving the binary status variables of interest; antenatal care up-take [yes = 1 (ANC visit ≥ 4)] and [no = 0 (ANC visit of ≤ 3]; facility delivery utilization [yes = 1 (facility delivery) and no = 0 (home delivery)], and the secondary outcome variables; stillbirth, perinatal and neonatal deaths, generated through the re-coding of the relevant variable *m14, m15, b6, b7*, and *s1015,* from the DHS data sets (Table 5).

The treatment difference will be determined through nearest-neighbor matching of treated and untreated units’ propensity scores generated ex-post, and using logistics regression while controlling for the confounding variables for precision. The 'free' policy impact will then be determined using the average treatment effect on the treated. Robustness of results will be achieved with reduced standard errors using bootstrapping replication while testing for sensitivity using a t-test of bias, and probit regression.

Of the treatment and comparison country analysis, the DID analysis will be used to determine the policy impact, using the 2008 data set of the two countries (Ghana and Kenya) as a baseline and 2014 data sets as the end line. The study is powered by the sample size calculation, originally determined by the survey design. The sample size is n = 2992/5884 (8,876) for Ghana DHS 2008/2014 data sets, and n = 6079/20,964 (27,043) for Kenya DHS 2008/2014 data sets respectively.

Clustering and stratification will be adjusted for using sample survey weighting at all stages of the analysis. This will produce unbiased treatment estimate that can be generalized to the original survey population [26, 52].

The qualitative data will be deductively analyzed using predefined themes. However, common themes that emerges from the interviews and focused discussion will be organized as sub-themes and inductively reported. The approach will be aided by NVIVO 12, through which nodes and their children will be created to categories significant statements into similarities and dissimilarities [73].

The results of the primary data will be reported using the common themes approach with word frequency count and cloud, and vivid quotations to back themes. The inclusion of qualitative data will add context and situate the discussion with explanatory power to the statistical findings [48].

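### The matching counts every Ghanaian birth in the 2014 survey round as treated, so its result is a before-after contrast and not the effect on policy recipients that its label claims

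*Protocol article*

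**What the plan says.** Study design in the protocol article is the only place that states the two matching groups: "the treated group, post-intervention (2014 DHS) and the untreated group, pre-intervention data (2008 DHS) for comparison using the observed characteristics". That section names the estimand as the average effect on the treated, and Data analysis repeats it: "The 'free' policy impact will then be determined using the average treatment effect on the treated". Data analysis also pools the two Ghana rounds: "For the matching method, Ghana’s DHS data sets (2008 and 2014) will be merged". None of these places limits the 2014 group to women who received the policy.

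Other sections define treatment by person:

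- Specific objectives, objective 3, concerns the effect of facility delivery on stillbirth, perinatal and neonatal death "among women who received the FMHCP program compared to those who did not receive the program".
- Operational definitions builds the treatment group from "Pregnant women study participants registered with the national health insurance scheme and made 4+ antenatal care visits or pregnant women participants in Ghana", the last part being those who delivered in a facility.
- Variables of interest (with Table 5) and Exposure variables make the mother's own insurance status, coded 0/1 from s1015, the main exposure and the proxy for the policy.

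The difference-in-differences is set out separately, by country and round: "The after treatment (end line) is also represented by Y_0_ and Y_1_ for Ghana DHS 2014 and Kenya DHS 2014, respectively". It is called a treatment effect and a policy impact, but never an effect on the treated. Demographic and health survey data adds that "the GDHS 2014 collected information on the free maternal health policy".

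**The concern.** An average effect on the treated must average over people who were treated. Under the round definition, a woman interviewed in 2014 who never enrolled is in the treated group, yet objective 3 needs her on the other side of the comparison. The estimate then describes what changed in Ghana between the two rounds after matching on observed characteristics. It does not describe what the policy did for women who received it.

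This affects interpretation most for the mortality outcomes. A null reported as an effect on the treated could be read as the policy failing in recipients, when part of it may be incomplete coverage. A positive result could equally be read as benefit to recipients when part of it is calendar change. Because three definitions of treatment coexist, two analysts following the article could also run different matchings and both claim to have followed it.

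**Working it through.** **Reproducing the article's figure.** Ghana 2008 plus Ghana 2014: 2,992 + 5,884 = 8,876, as stated. The merged sample is both rounds in full, with no restriction by receipt.

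**Was receipt universal in the years behind the 2014 round?** The article describes participation as open and voluntary. Table 1 gives enrolment of 485,460 in 2011 and 754,658 in 2012.

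- Rise on the 2011 base: (754,658 − 485,460) / 485,460 = 55%. The table prints 36% because it divides by the later year: 269,198 / 754,658.
- If 2012 enrolment were every eligible pregnancy and that number were constant, 2011 receipt would be 485,460 / 754,658 = 64%. With an assumed 3% growth it would be 66%.

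Universal receipt is therefore implausible. The 2014-round share itself cannot be derived, since Table 1 has no denominator and no 2014 row.

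**What the round contrast estimates.** Let c be the share of the 2014 round that received the policy. Assume no receipt in the 2008 round and no effect on non-recipients. Then

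contrast = c × (effect in recipients) + calendar change.

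The values of c below are assumed. Non-recipients counted as treated = 5,884 × (1 − c). The sample-size factor for equal power is 1/c². Power is two-sided at 0.05 for 2,992 against 5,884 with no calendar change, ignoring the survey design effect and matching losses. Two illustrations are used: an assumed 5-point gain in utilization from an assumed 55%, and an assumed reduction of 9 per 1,000 in neonatal death from the article's 30 per 1,000.

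| c | Non-recipients counted as treated | Utilization contrast (points) | Power | Neonatal contrast (per 1,000) | Power | Sample-size factor |
|---|---|---|---|---|---|---|
| 1.0 | 0 | 5.0 | 0.995 | 9.0 | 0.73 | 1.00 |
| 0.9 | 588 | 4.5 | 0.98 | 8.1 | 0.64 | 1.23 |
| 0.7 | 1,765 | 3.5 | 0.88 | 6.3 | 0.43 | 2.04 |
| 0.5 | 2,942 | 2.5 | 0.61 | 4.5 | 0.24 | 4.00 |

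**Direction.** At c = 0.7 with a 5-point effect in recipients:

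- no trend: 0.7 × 5 = 3.5 points, an understatement;
- upward trend of 1.5 points: 3.5 + 1.5 = 5.0, equal to the recipient effect by coincidence;
- upward trend of 3 points: 3.5 + 3 = 6.5, an overstatement.

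The label is wrong in all three cases, but the sign of the error is not determined.

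**Do the person-level definitions resolve it?** Operational definitions splits women by antenatal visits or place of delivery. Its comparison group includes insured women with fewer than four visits, so it does not isolate non-recipients. Variables of interest uses insurance status, but nothing says that this variable forms the matching groups. Data analysis refers to treated and untreated units without redefining them. Study design is the only explicit statement, and it uses survey round.

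**The case against.** **The difference-in-differences is sound on this point.** The policy was aimed at every pregnant woman in Ghana, so comparing whole countries by round is an ordinary policy-level effect, and objective 2 asks for a Ghana–Kenya comparison. A reader might infer that this analysis too is mislabelled or wrongly diluted. The article does not support that, since it attaches the effect-on-the-treated label to the matching only. This objection stands in full.

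**Dilution and its size are not established.** A reader might infer from Table 1 that 15% to 32% of the recipient effect is lost. Taking 2013 enrolment as full coverage does give 2,518,736 / (4 × 774,009) = 81% for 2010–2013 and 2,901,952 / (5.5 × 774,009) = 68% from mid-2008, or 85% and 73% with 3% yearly growth in pregnancies. But the denominator is assumed, and calendar change can offset or exceed the loss in the matching. This objection also stands.

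**Scaling by coverage does not answer objective 3.** Objective 3 and research questions 2 and 3 concern the effect of facility delivery. Dividing the difference-in-differences by the receipt share gives a policy effect in recipients, and it restores no power. This stands too.

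**Person-level definitions exist elsewhere.** They do, so the defect is partly an unreconciled contradiction over who is treated. They do not remove it, because no section carries them into the matching.

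**Conclusion.** The point holds for the matching. As written, its treated group is the whole Ghana 2014 round, its result is a population-level before-after contrast, and calling that the average effect on the treated is wrong. The round definition also contradicts the two person-level definitions. This conclusion rests on the article's wording and on receipt being less than universal, which voluntary participation and the 55% enrolment jump in one year make very likely.

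No size or net direction can be given from the documents. The tabulated range is conditional on assumed coverage of 0.5 to 0.9, assumed effects, no calendar trend and simple random sampling. The difference-in-differences needs a clearer description and no redesign.

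**What to change.** 1. Reconcile Operational definitions, Study design, Variables of interest, Exposure variables and Data analysis on one treatment definition for the matching.
2. If an effect on the treated is wanted, define treated by individual receipt, using the policy item in the 2014 Ghana survey or the s1015 insurance proxy. Take 2014 non-recipients as comparators, with a propensity score that models selection into enrolment.
3. If the 2014-versus-2008 contrast is kept, relabel it a population-level before-after effect and drop the effect-on-the-treated wording.
4. For objective 3 and research questions 2 and 3, estimate the facility-delivery effect separately in recipients and non-recipients, and compare the two.
5. Keep the difference-in-differences, described as the country-level effect of introducing the policy. Report beside it the weighted share of 2014 births whose mothers received the policy, so that a null is not read as no effect in recipients. A coverage-scaled version is at most an optional sensitivity analysis under a stated no-spillover assumption.

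The cost is wording in a few sections, one weighted proportion and a re-specified matching on data already held. The downsides are real. A receipt-based comparison is open to selection into enrolment. It also uses fewer treated women: at an assumed 70% coverage, 4,119 treated against 1,765 comparators (5,884 in all), and the merged 8,876 would no longer be the matching sample.

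### The propensity score match sets Ghana 2014 against Ghana 2008, so its policy effect includes all between-round change that the matched covariates do not carry

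*Protocol article*

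**What the plan says.** All references are to the protocol article.

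- **Who is matched.** Study design names the two matching groups as "the treated group, post-intervention (2014 DHS) and the untreated group, pre-intervention data (2008 DHS) for comparison using the observed characteristics". Data analysis confirms that Kenya plays no part: "For the matching method, Ghana’s DHS data sets (2008 and 2014) will be merged".
- **What the result is called.** Data analysis takes the average treatment effect on the treated, from nearest-neighbour matching, as the policy impact. A separate paragraph there uses the Ghana/Kenya difference-in-differences (DID) for the same purpose.
- **How the effect is defined elsewhere.** Statistical methods and rationale, with Table 2, sets T = Y0 − X0 for Ghana and C = Y1 − X1 for Kenya, and gives the treatment effect as T − C.
- **What merging is said to do.** Data analysis: "This will increase the sample size to n = 8876, and add power to the study", and "The merger will also eliminate the risk of lack of common support, the so-called curse of dimensionality". Statistical methods and rationale is milder: "this study will merge the 2008/2014 data sets to increase the sample size and to minimize the risk of the curse of dimensionality".
- **How the two methods relate.** "The combined effect of the two quasi-techniques will eliminate the limitation of one and enhance the robustness of the study results".
- **Standard errors.** "Robustness of results will be achieved with reduced standard errors using bootstrapping replication".
- **Other definitions of treatment.** Variables of interest and Exposure variables make the woman's own insurance status the exposure, coded 0/1 in Table 5. Operational definitions builds the groups from insurance registration with antenatal visits, or from facility delivery.

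**The concern.** On the Study design definition, treatment and calendar time are the same variable: every treated woman was surveyed in 2014 and every untreated woman in 2008. Matching can balance age, education, wealth, residence and similar factors between the rounds. It cannot balance anything else that changed in Ghana over those years, because no 2014 woman serves as a control. The plan relies on assuming that unobserved differences cancel, which is hard to defend between groups about six years apart. Its own Background faults earlier work for reporting rises in attendance without regard to factors that vary over time.

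At stake is one of the two estimates that the plan reads as policy impact. If utilization was rising, or mortality falling, for other reasons, the matched estimate would credit the policy with that change. The statements about merging and bootstrapping make this estimate look better supported and more precise than the design allows.

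**Working it through.** **1. The plan's own figure.** Inputs from Data analysis: "The sample size is n = 2992/5884 (8,876) for Ghana DHS 2008/2014 data sets". 2992 + 5884 = 8876, so the stated total is correct.

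**2. What the merger adds.**

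| Treatment defined by | Untreated | Treated | Effect of merging |
|---|---|---|---|
| Survey round (Study design) | all 2992 from 2008 | all 5884 from 2014 | neither arm gains a record; the merged file is the comparison itself |
| Insurance status (Variables of interest, Exposure variables) | possible in both rounds | possible in both rounds | records rise from 5884 (2014 alone) to 8876 |

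The claim of added power fits only the second row. The matching groups are defined by the first.

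**3. Which quantity is estimated.** Let X0* be the Ghana 2008 outcome after matching to the 2014 covariate mix.

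- Matched estimate: T* = Y0 − X0*.
- The plan's effect on the same covariate footing: T* − C*, where C* is the Kenya change after the same adjustment.
- Difference: T* − (T* − C*) = C*.

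If parallel trends holds after adjustment, the bias of the matched estimate is C*, the covariate-adjusted comparison-country change. The documents give no value for it.

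**4. Does matching remove the trend?** Simulation with 200 replicates of 2992 against 5884, nearest-neighbour matching with replacement on one covariate, assumed baseline utilization 55%, and a true policy effect of zero. The trend is the part not carried by the covariate. Trend sizes and covariate shift are assumptions.

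| Covariate shift | Trend (points) | Unmatched difference | Matched effect |
|---|---|---|---|
| none | 0 | 0.1 | 0.1 |
| none | 5 | 5.0 | 5.0 |
| none | 10 | 9.9 | 9.9 |
| 0.3 SD | 0 | 3.0 | 0.1 |
| 0.3 SD | 5 | 8.1 | 5.0 |
| 0.3 SD | 10 | 13.0 | 9.8 |

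Matching takes out the compositional part (about 3 points here) and leaves almost all of the rest.

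**5. Chance of a false finding.** Take an assumed 60% baseline, a 5-point residual trend, no policy effect, and the plan's 0.05 level (two-sided assumed). Power = Φ[(0.05 − 1.96·SE0)/SE1], with SE0 from the pooled proportion and SE1 from the separate proportions.

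- SE1 = √(0.60×0.40/2992 + 0.65×0.35/5884) = 0.01090.
- Pooled proportion = (0.60×2992 + 0.65×5884)/8876 = 0.633, so SE0 = 0.01082.
- (0.05 − 0.02121)/0.01090 = 2.64, which gives 99.6%.

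Multiplying both variances by assumed design effects of 1.5 and 2 gives 96.4% and 90.3%. This is approximate, because it ignores the extra variance from reusing controls.

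**6. Common support.** With one covariate built so that 10%, 20% or 30% of the treated lie beyond the untreated range, the off-support share stayed at about 10%, 20% and 30% at totals of 4438, 8876 and 26,628. A larger file fills sparse regions of the score; it does not create overlap where there is none.

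**7. Bootstrap.** Resampling estimates the variability that an estimator already has. A smaller bootstrap standard error is not a gain in precision, so it cannot serve as evidence of robustness.

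**The case against.** The strongest reply is that the cross-round definition stands in one section only. Variables of interest, Exposure variables and Table 5 code exposure for each woman, and the third specific objective compares women who received the programme with those who did not. On that reading untreated women exist in 2014, merging does add records, and trend enters only as far as coverage differs between rounds. This stands as a limit on the point, not as an answer to it: Study design is the explicit statement of who is matched with whom, and the article never reconciles the two.

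A second reply is that the DID is there to remove shared trend and that the methods are meant to compensate for each other. But each is described as yielding its own policy impact, so the DID leaves the matched estimate as it is.

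The plan also deserves credit for naming lack of common support as a drawback and for stating the unobserved-differences assumption openly under Statistical assumptions.

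A reader might infer more than the documents support:

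- *The whole six-year trend is counted as policy effect.* No. The part carried by matched covariates is removed (step 4).
- *The bias is the raw Kenyan change, or the two methods must disagree.* No. The relevant quantity is the adjusted change, under parallel trends; if it is near zero the two agree.
- *At most 2992/5884 = 50.8% of treated women can be matched.* Only under one-to-one matching without replacement, which the plan does not state. Replacement and caliper rules can be left to a fuller document.
- *The bootstrap ignores clustering.* Not supported. The resampling unit is not given, and Sample weighting names bootstrapping as a means of adjusting for clustering and stratification.

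**Conclusion.** The point holds in this form. As Study design defines it, the matched estimate is a covariate-adjusted before-after difference in Ghana and should not by itself be called policy impact. Its bias is whatever change between rounds the matched covariates do not carry. That equals the adjusted comparison-country change if parallel trends holds.

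The documents do not give the size. An assumed residual trend of 5 to 10 points passes almost fully into the estimate, and 5 points would be declared significant about 90% to 99.6% of the time at design effects of 2 down to 1. These figures rest on assumed trends, baselines and design effects and concern utilization. No size was worked out for the mortality outcomes, where the same mechanism applies.

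Three further statements need correcting. The treatment definition conflicts between sections. Merging adds no power to the cross-round comparison and, under any definition, cannot eliminate lack of support. Bootstrapping does not reduce standard errors.

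**What to change.** 1. Reconcile the treatment definition across Study design, Operational definitions, Variables of interest and Exposure variables, so that one definition governs the matching.
2. Combine the two methods. Use the propensity score to weight or match Ghana 2008, Kenya 2008 and Kenya 2014 to Ghana 2014, and report the weighted DID (T − C) as the policy effect. Use standard errors that respect the primary sampling units, for example weighting with a bootstrap of whole units.
3. If the cross-round Ghana match is kept, label it an adjusted before-after difference.
4. If women are instead matched by individual insurance status within the 2014 round, state the self-selection limitation, since the plan itself describes participation as fairly open and voluntary.
5. Delete the claims that merging eliminates lack of support and adds power to the cross-round comparison, and that bootstrapping reduces standard errors.

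**Cost.** All four data sets are already part of the plan, so the change is to analysis code and wording. Intervals will probably be wider. The weighted DID still depends on parallel trends between Ghana and Kenya.
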